### Participant timeline

A Case Report Form (CRF) form will be established and completed for each enrolled patient, with follow-up visits scheduled every 12 weeks (±2 weeks) at baseline and throughout the treatment period. Clinical symptoms and signs will be observed during each follow-up visit, and peripheral blood PBMC and plasma specimens will be collected and stored at −80°C for future research. The clinical test items at the follow-up visit are shown in Figure 3.

**Figure 3 fig3:**
[figure not shown]
Schedule of enrollment and follow-up.

### Sample size

Since there are no existing literature reports on Peg-IFN treatment for combined MAFLD in the CHB-advantaged population, the sample size for this study is based on the results of our team’s previous research. In that study, Peg-IFN treatment of CHB and CHB combined with MAFLD patients for 48 weeks resulted in HBsAg clearance rates of 35 and 60%, respectively. Given the lack of established data in this specific population, we chose to use this estimate as it is reflective of our previous work, which involved similar patient profiles and treatment conditions. Setting the test level at *α* = 0.05 and the power of the study (1-*β*) at 0.90, the required sample size was calculated using the test module for two independent sample rates in PASS 11.0. The calculation indicated that 79 patients should be enrolled in each group. Considering a 15% dropout rate, 92 participants are needed in each group, thus expanding the sample size to 100 cases per group.

### Recruitment

Participants will be recruited from four medical centers in Beijing and Hebei, China: Beijing You’an Hospital of Capital Medical University, Fifth Medical Center of General Hospital of the People’s Liberation Army, Beijing Ditan Hospital of Capital Medical University, and Baoding People’s Hospital. Each hospital will have a study coordinator to facilitate and coordinate the trial. Patients will be informed of the study’s purpose, procedures, and potential risks and benefits. Written informed consent will be obtained from all participants. They will also be allowed to withdraw from the trial at any time without any consequences.

Patients will be invited to participate in this study shortly after diagnosis. At the screening follow-up, a clinically experienced researcher (physician) will confirm eligibility for enrollment by reviewing symptoms, laboratory results, and imaging such as ultrasound or CT, ensuring that each inclusion and exclusion criterion is met. Recruitment will occur over 24 months, from January 2024 to December 2025.

No patients or members of the public other than professional clinicians and researchers were involved in the design, conduct, reporting, or dissemination plans for this study.

## Methods: data collection, management, and analysis

### Plans for assessment and collection of outcomes

Data will be collected using specially designed paper-based CRFs. Once completed, these forms will be entered into a database by designated personnel after prior data inspection. The Schedule of enrollment and follow-up (Figure 3) provides a detailed illustration of both the schedule and the specific nature of data collection required throughout the study period.

### Plans to promote participant retention and complete follow-up

Upon study completion, if a patient achieves HBsAg seroclearance, this outcome is considered the optimal result approaching “clinical cure,” indicating significantly improved long-term prognosis. For such cases, our research team will develop a follow-up monitoring and health management plan to maintain the therapeutic effect. Conversely, if HBsAg seroclearance is not achieved, clinicians will tailor the treatment strategy based on the patient’s specific health condition, aiming to optimize therapeutic outcomes and continue to control disease progression. Regardless of treatment outcomes, we are committed to providing patients with the most suitable personalized follow-up care to ensure they receive optimal health support.

### Data management

The number of sample cases in this subject is large, and the nodes of retained specimens and test items are more, in order to ensure the uniformity and accuracy of the test, we take the following measures: in the process of specimen retention and separation, there are people responsible for the registration, sampling, separation of cells and serum, and freezing; specimens retained at different time nodes are uniformly detected by the specialized inspectors to ensure the reliability and accuracy of the test results. Trial data were collected and stored in accordance with GCP guidelines [China National Medical Products Administration, National Health Committee. Notice on the publication of Good Clinical Practice (no. 57 of 2020). April 26, 2020 (in Chinese). https://www.nmpa.gov.cn/directory/web/nmpa/xxgk/ggtg/ypggtg/ypqtggtg/20200426162401243.html]. Final approval of the research database will only be granted after successful implementation of these protocols has been confirmed.

### Statistical methods for primary and secondary outcomes

#### Primary outcomes

The Kaplan–Meier method was used to estimate the cumulative incidence of HBsAg seroclearance, and the log-rank test was used to compare the cumulative probabilities of different subgroups.

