## Methods: subjects, interventions, and outcomes

### Study setting

This prospective, multicenter, open cohort study will include HBV-infected patients from four large tertiary hospitals in North China. A total of 200 participants are planned, comprising 100 patients with CHB and 100 patients with CHB combined with MAFLD. We used the SPIRIT checklist when writing our report (17). The Institutional Review Board of Beijing You’an Hospital affiliated with Capital Medical University approved the trial protocol (version 9.1, reference number LL-2024-051-K, dated May 10, 2024).

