### Outcome

Primary outcome indicators: 48-week HBsAg clearance rate. Secondary outcome indicators: 48-week HBsAg quantitative decline, HBV DNA undetectable rate, HBsAg serologic conversion rate, Peg-IFN adverse reactions.

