### Methods for any additional analyses

SPSS 27.0 statistical software was used for data analysis. Categorical variables were expressed as counts and percentages, while continuous variables were expressed as mean and standard deviation. Clinical data were statistically analyzed using the Kruskal-Wallis test. Variance homogeneity across groups was assessed for each test index. If the variance was homogeneous, the LSD method of one-way ANOVA was applied; if the variance was not homogeneous, the Kruskal-Wallis test was used for comparisons across multiple groups. For comparisons between the two groups, the Mann–Whitney *U* test was employed. Immunological data, including HBsAg levels, HBV DNA titers, and immune marker levels (e.g., T-cell responses, cytokine profiles), will be analyzed using appropriate statistical methods based on the data distribution. Descriptive statistics (mean, SD, median, and IQR) will be used to summarize the data. For longitudinal analysis of immune markers (such as HBsAg clearance and T-cell responses) over the course of treatment, mixed-effects models will be employed to account for repeated measures and correlations within subjects. If immunological data are not normally distributed, non-parametric tests such as the Mann-Whitney U test (for comparisons between two independent groups) or the Kruskal-Wallis test (for comparisons across more than two groups) will be used. Cox proportional hazards regression will be utilized to assess the relationship between immunological markers (e.g., HBsAg clearance, T-cell response) and clinical outcomes, such as sustained HBsAg seroclearance or progression to clinical cure. In addition, we will conduct correlation analyses (Spearman’s rank correlation) to explore potential associations between immune parameters (e.g., cytokine levels, T-cell counts) and clinical variables (e.g., liver function, ALT/AST levels). A *p*-value of <0.05 was considered statistically significant.

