## Discussion

The prevalence of MAFLD is steadily increasing both in the general population and among patients with CHB worldwide. Although fatty liver is recognized as a risk factor for adverse liver outcomes, including cirrhosis and hepatocellular carcinoma, its interactions with HBV and the resulting clinical effects remain complex and not fully understood.

Some studies have identified fatty liver as an unfavorable factor affecting antiviral efficacy. In a study of 213 Chinese patients with CHB treated with entecavir (ETV), the rate of HBV DNA undetectability at 24 weeks was significantly lower in patients with comorbid steatosis compared to those without hepatic steatosis (47.7% vs. 58.8%, *p* = 0.01) (18). Additionally, in a study of 89 HBeAg-positive CHB patients treated with Peg-IFN for 48 weeks, those with comorbid steatosis had significantly lower HBV DNA undetectability rates 48 weeks after discontinuation compared to those without steatosis. Multifactorial analysis showed that steatosis was an unfavorable factor for sustained viral response (OR = 0.012, *p* = 0.02) (19). The EFFORT study suggests that new-onset and persistent MAFLD in patients with HBeAg-positive CHB treated with NA may counteract the benefits of antiviral therapy, reduce the rate of ALT normalization, and negatively influence fibrosis improvement (20).

In contrast, some studies have shown that patients with hepatic steatosis are more likely to achieve HBsAg clearance. The metabolic components and immune alterations associated with MAFLD progression may directly inhibit HBV replication or indirectly induce antiviral immune responses. In patients with chronic HBV infection, comorbid MAFLD has been found to inhibit HBV replication and is associated with spontaneous HBsAg clearance (21). An international multicenter randomized controlled study of 4,769 patients with treatment-naïve CHB, treated with either entecavir (ETV) or tenofovir (TDF), with a median follow-up time of approximately 5.16 years, found that 58 patients achieved HBsAg clearance, and hepatic steatosis was identified as a favorable factor for HBsAg clearance (HR = 1.84) (22). Additionally, a previous study by our group showed that the 96-week HBsAg clearance rate was higher in inactive HBsAg carriers with moderate steatosis compared to those without steatosis (23).

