Sequencing of immune cells, such as T lymphocytes and DC cells, from liver cancer patients has revealed the characteristics of immune cells within the liver cancer environment, aiding in the development of more effective immunotherapeutic targets (33). However, the application of single-cell sequencing technology in populations with CHB combined with MAFLD has not yet been explored, particularly in investigating the mechanisms involved in HBsAg clearance. In this study, we aim to use transcriptome single-cell sequencing to explore the immunomolecular mechanisms of HBsAg clearance in CHB patients with MAFLD who are receiving Peg-IFN treatment. This approach will provide a multi-stage, dynamic, and high-resolution immune landscape of the HBsAg clearance process, clarify the gene regulation of immune cells during HBsAg clearance, uncover the immune cytogenetic basis of this clearance, and identify the molecular immunogenetic markers that determine successful HBsAg clearance. In addition, although this study has adopted a prospective and multicenter study protocol to reduce sampling and follow-up bias, there are still some limitations: (1) Given that the study is multicenter and cohort-based, there may be variability in treatment outcomes due to differences in patient populations, hospital settings, and clinician practices. While we aim to include a representative sample, the findings may not be generalizable to all HBV patients, particularly those outside of the study centers or those with more advanced liver disease. (2) The study relies on patient adherence to treatment protocols, including Peg-IFN therapy, and the potential for non-compliance or early dropout could impact the results, particularly the achievement of HBsAg clearance. (3) While we will attempt to control for common confounding factors such as age, gender, and baseline liver function, there may be other unmeasured factors (e.g., genetic predispositions, lifestyle habits, or co-infections) that could influence the treatment response and the success of Peg-IFN therapy.

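### The primary MAFLD comparison is stated only as Kaplan-Meier with a log-rank test, and no stated analysis of clearance by MAFLD carries out the confounder control that the article promises

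*Protocol article*

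**What the plan says.** **Design.** Study setting: "This prospective, multicenter, open cohort study will include HBV-infected patients from four large tertiary hospitals in North China", "comprising 100 patients with CHB and 100 patients with CHB combined with MAFLD". Group membership is a patient's disease status; nothing is allocated.

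**Primary outcome.** Outcome: "Primary outcome indicators: 48-week HBsAg clearance rate".

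**Primary analysis.** Under Primary outcomes, Kaplan-Meier estimates cumulative seroclearance and "the log-rank test was used to compare the cumulative probabilities of different subgroups". No covariates, strata, matching or weights are named.

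**Other models.** Under Secondary outcomes, a mixed model and GEE describe HBsAg levels over time by group. Under Methods for any additional analyses, "Cox proportional hazards regression will be utilized to assess the relationship between immunological markers (e.g., HBsAg clearance, T-cell response) and clinical outcomes". Neither addresses clearance by MAFLD status.

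**Confounding.** The limitations at the end of the Discussion say: "While we will attempt to control for common confounding factors such as age, gender, and baseline liver function", and then warn of unmeasured factors. They also expect "variability in treatment outcomes due to differences in patient populations, hospital settings, and clinician practices".

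**The concern.** The stated aim is the impact of MAFLD on the response to Peg-IFN, and the result is meant to help clinicians select patients and adjust treatment. Without randomisation, an unadjusted comparison mixes any MAFLD effect with whatever else differs between the groups. The article recognises this in its limitations, but its methods sections contain no step that acts on it for the primary outcome.

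The article's own text makes some imbalance plausible:

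- BMI of 23 kg/m² or more is one of three routes to a MAFLD diagnosis (Eligibility criteria), and the Peg-IFN dose depends on body weight (Intervention description). The groups can be expected to differ in weight and in dose received.
- The Introduction treats a low HBsAg level as the mark of patients suited to clearance. The Discussion reports that "comorbid MAFLD has been found to inhibit HBV replication and is associated with spontaneous HBsAg clearance", so baseline HBsAg may differ by group.
- Centre differences are acknowledged but have no place in the stated analysis.

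At stake is whether a significant result can be attributed to MAFLD, and whether a null result can be taken as no effect.

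**Working it through.** **1. The plan's own figure.** Inputs from Sample size: 35% and 60% clearance, α = 0.05 (taken as two-sided), power 0.90. With unpooled variance,

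n = [p₁(1−p₁) + p₂(1−p₂)] (z₀.₉₇₅ + z₀.₉₀)² / (p₂−p₁)² = (0.2275 + 0.2400)(1.960 + 1.282)² / 0.25² = 78.6, so 79 per group.

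This matches the stated 79. Dividing by 0.85 gives 92.9, so 93 against the stated 92, an immaterial difference. The calculation is a crude comparison of two rates with no allowance for covariates. With 100 enrolled and 15% dropout, 100 × 0.85 = 85 per group are evaluable.

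**2. Promise against method.**

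| Stated analysis | What it addresses | Adjusts clearance by MAFLD? |
|---|---|---|
| Kaplan-Meier and log-rank | HBsAg clearance | No covariates or strata stated |
| Mixed model, GEE | HBsAg level over time (secondary) | No |
| Cox regression | Immunological markers and outcomes | No |

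**3. Illustration with baseline HBsAg.** The documents give none of these inputs, so all are assumed: log10 HBsAg normal with mean 2.5 and SD 0.6 in the CHB group, truncated at log10(1500) because of the entry limit; 35% clearance in that group; log-odds of clearance falling by 1 to 2 per log10; no MAFLD effect; 85 per group; two-sided 5% test of two proportions. The mean before truncation is set 0.2 or 0.4 lower in the MAFLD group. Truncation shrinks the realised difference in means to 0.14 or 0.30.

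| Realised difference (log10) | Slope | Spurious difference (points) | Rejection |
|---|---|---|---|
| 0.14 | 1 | 3.2 | 7% |
| 0.14 | 2 | 5.8 | 12% |
| 0.30 | 1 | 6.9 | 15% |
| 0.30 | 2 | 12.4 | 37% |

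**4. Second check, using the log-rank test itself.** Assumed: one binary prognostic factor, no MAFLD effect, visits at weeks 12, 24, 36 and 48, 85 per group, 2,000 simulated trials.

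| Clearance without / with the factor | Prevalence, CHB / MAFLD | Unadjusted log-rank rejects | Stratified log-rank rejects |
|---|---|---|---|
| 35% / 60% | 50% / 50% | 5% | 5% |
| 35% / 60% | 40% / 60% | 10% | 4% |
| 35% / 60% | 30% / 70% | 28% | 6% |
| 25% / 70% | 40% / 60% | 22% | 5% |
| 25% / 70% | 30% / 70% | 67% | 5% |

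**5. Power after adjustment.** If covariates explain a share R² of the variance of MAFLD status, the effective size is about 85(1 − R²) per group. For 35% against 60% (pooled-variance test):

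| R² (assumed) | Effective n | Power |
|---|---|---|
| 0 | 85 | 91% |
| 0.05 | 80.75 | 90% |
| 0.10 | 76.5 | 88% |
| 0.20 | 68 | 84% |
| 0.30 | 59.5 | 79% |

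This ignores any precision gained from prognostic covariates.

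**The case against.** **The article condenses a fuller protocol.** Covariate lists and model forms are commonly left to that document or to an SAP, and the limitations do commit to confounder control. This stands as far as the exact list is concerned. It does not remove the point, because the article fixes a primary method, assigns its regression models to other questions, and leaves its own promise without a method.

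**The primary-analysis text speaks only of subgroups.** True, but the objective and primary outcome leave MAFLD against no MAFLD as the main comparison.

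**Entry limits restrict imbalance.** HBsAg below 1,500 IU/mL, HBeAg negativity and HBV DNA below 10 IU/mL apply to both groups. This limits imbalance in HBsAg without removing it.

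**Adjustment can remove part of the effect.** The Abstract says MAFLD may influence transaminase levels, and the Discussion reports that it suppresses HBV. Baseline ALT and HBsAg may therefore partly be consequences of MAFLD, and adjusting for them moves the question from a total towards a direct effect. This stands and shapes the fix.

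Four stronger readings are tempting, and the documents do not support them:

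- That imbalance *will* pass for a MAFLD effect. No baseline data are given. The evidence cited on MAFLD and spontaneous clearance concerns chronic infection generally, not NA-suppressed patients on Peg-IFN, and the Discussion also reports opposite and null findings.
- That a log-rank test cannot adjust. It can be stratified, as step 4 shows; the plan just does not say so.
- That baseline HBsAg has been ruled out as a confounder. The list in the limitations is given as examples and is open.
- That only a p-value will result. Kaplan-Meier gives clearance by group, hence an unadjusted difference.

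**Conclusion.** The point holds: the promised control of confounding has no counterpart in any stated analysis of clearance by MAFLD, so following the plan as written can give a confounded answer to the primary question. The direction and size of any bias cannot be known from the document.

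The range of about 3 to 12 points and 7 to 37% rejection rests wholly on assumed inputs, and its low end is small. The binary-factor check shows the same mechanism under different assumptions and shows that simple stratification holds the error near 5%. The effect on power is secondary: the Sample size section openly describes a two-rate calculation, and at modest R² the planned enrolment keeps power between 84% and 90%.

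**What to change.** 1. Under Primary outcomes, prespecify a covariate-adjusted estimate of the MAFLD effect on 48-week clearance, with a 95% CI, as the main result. Cox regression, logistic regression with standardisation to a risk difference, or propensity weighting would each serve; choose one in advance.
2. Name the covariates beforehand: age, sex, specified measures of baseline liver function, and centre.
3. Report the estimate with and without baseline log10 HBsAg and ALT, and say that the two answer different questions if these lie on the MAFLD pathway.
4. State how body weight and weight-based dose are handled in the analysis, given that BMI is part of one route to MAFLD.
5. Keep Kaplan-Meier and the log-rank test as the unadjusted description.
6. In Sample size, say that 90% power refers to the unadjusted two-rate comparison, and give the adjusted range with its assumed R².

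The expected number of clearances is 85 × (0.35 + 0.60) = 80.75. With one liver-function measure, the smaller model has 7 parameters (MAFLD, age, sex, liver function, three for centre), or 11.5 clearances each. Adding HBsAg and ALT makes 9 parameters, or 9.0 each. Both are workable.

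The cost is wording. HBsAg and liver biochemistry are already among the baseline tests. The downside is a slightly lower stated power. The text should be settled before the efficacy analyses, including the early look at patients who have completed 48 weeks described under Interim analyses.

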#### Secondary outcomes

A linear mixed-effects model was employed to analyze the trends in HBsAg levels over time. Random effects were included to account for inter-individual variability among patients. Fixed effects in the model included time (measured in months), group classification (e.g., responder vs. non-responder, MASLD group vs. non-MASLD group, male vs. female), and the interaction between time and group classification. Additionally, marginal effects of changes in HBsAg levels over time for different groups were estimated using generalized estimating equations (GEE). This approach provided a comprehensive assessment of the temporal variation in HBsAg levels across various patient subgroups.

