### Eligibility criteria

Inclusion Criteria:

Chronic Hepatitis B (CHB): Meets the 2022 Guidelines for the Management of Chronic Hepatitis B: (1) HBsAg positive for >6 months; (2) On NA treatment; (3) HBsAg <1,500 IU/mL; (4) HBeAg negative; (5) HBV DNA <10 IU/mL.Metabolism-Associated Fatty Liver Disease (MAFLD):

(1) Diagnosis of hepatic steatosis confirmed by abdominal ultrasound, Fibroscan, or liver steatosis measurement via MRI. Steatosis is categorized as mild, moderate, or severe based on the thresholds of the above tests. (2) Additionally, the patient must meet one of the following three conditions: ①. Overweight or obesity (BMI ≥ 23 kg/m^2^); ②. Diabetes mellitus; ③. Lean or normal-weight patients meeting at least 2 metabolic abnormalities (e.g., Figure 2).

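### HBsAg decline is to be modelled on HBsAg levels with no log scale, no baseline term and no rule for values below the assay limit; fitted as worded, the group-by-time term would mainly reflect baseline level

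*Protocol article*

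**What the plan says.** The Outcome section lists "48-week HBsAg quantitative decline" first among the secondary outcomes. It does not say whether the decline is absolute or on a log scale.

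Under Statistical methods for primary and secondary outcomes, the Secondary outcomes paragraph gives the model: "A linear mixed-effects model was employed to analyze the trends in HBsAg levels over time". Random effects allow for differences between patients. The fixed effects are time in months, a group classification (MASLD or not, responder or not, sex), "and the interaction between time and group classification". A GEE on the same levels is added for marginal effects. No transformation, baseline HBsAg covariate or assay limit is mentioned.

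Methods for any additional analyses puts HBsAg levels among the immunological data, whose method is to follow the distribution. The fallback named for non-normal data is Mann-Whitney or Kruskal-Wallis.

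Two other sections bear on this. Eligibility criteria require "HBsAg <1,500 IU/mL", with no lower bound beyond being HBsAg positive. The Sample size section reports that earlier work by the team "resulted in HBsAg clearance rates of 35 and 60%, respectively" for CHB and CHB with MAFLD.

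**The concern.** HBsAg at entry can lie anywhere from barely detectable to 1,500 IU/mL. On the IU/mL scale a patient cannot fall by more than the baseline value. A patient who clears from 100 IU/mL falls by about 100. One who does not clear but goes from 1,400 to 700 falls by 700, so a linear slope on that scale ranks the second above the first.

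Two things follow if the model is fitted to levels. A real difference in clearance between the groups is largely invisible, because most of the variation in slopes comes from where patients started. And a difference in starting level appears as a difference in decline. The cohort is not randomised and the listed fixed effects contain no baseline HBsAg, so nothing in the model removes such a difference.

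In addition, every patient who clears ends at the assay floor, where the recorded value depends on a reporting rule that the article does not give. What is at stake is the answer on the first secondary outcome: whether MAFLD changes the size of the HBsAg fall.

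**Working it through.** **1. Planning rates and share at the floor.** With 35% versus 60%, two-sided alpha 0.05 and power 0.90, the unpooled normal formula gives n = (1.960 + 1.282)² × (0.35 × 0.65 + 0.60 × 0.40) / 0.25² = 10.51 × 0.4675 / 0.0625 = 78.6, so 79 per group. This is the article's figure, so the rates are read as intended. The Study setting section plans 200 patients, "comprising 100 patients with CHB and 100 patients with CHB combined with MAFLD". At these rates 35 + 60 = 95 of 200, or 47.5%, would have cleared by week 48.

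**2. What a given response looks like in IU/mL.** A one-log10 fall is 1,500 − 150 = 1,350 IU/mL from a baseline of 1,500, but 10 − 1 = 9 IU/mL from a baseline of 10. The same proportional response differs 150-fold (1,350 / 9).

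**3. Simulation.** The visits (baseline and weeks 12, 24, 36, 48) and the clearance rates are the article's. The following are assumptions, because the article gives no figures for them:
- assay limit 0.05 IU/mL;
- baseline log10 HBsAg with mean 2.0 to 2.5 and SD mainly 0.6 (0.3 and 0.9 also tried), cut off at log10(1,500);
- patients who do not clear fall by 0.3, 0.6 or 1.0 log10 on average, or all patients follow a continuous distribution of decline;
- clearance either independent of baseline or more likely at low baseline.

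Each patient's least-squares slope was computed and group means were compared at the 5% level. This stands in for the time-by-group term of a balanced random-slope model. Runs used 100 or 85 patients per group; 85 is 100 less the article's 15% dropout.

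| Scenario | IU/mL: trials rejecting | log10: trials rejecting |
|---|---|---|
| Equal baselines, clearance 35% vs 60% | about 5-10% | about 87-98% |
| MAFLD baseline 0.3 log10 lower, same clearance or same log decline | about 57-72% | 7-11% (about 5% with baseline adjustment) |
| MAFLD baseline 0.3 log10 lower, clearance 35% vs 60% (100 per group, baseline means 2.3 and 2.0) | 38-70%, mean difference in the wrong direction | 65-82%, right direction |

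In the third row the IU/mL slopes differ on average by 4.6 to 8.1 IU/mL per month, with the MAFLD group falling more slowly although it clears more often.

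**4. Why.** Baseline level explains 69-98% of the variance of the individual slopes on the IU/mL scale and 1-21% on log10.

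**5. The floor by itself.** With log10 values and the floor value simply substituted, rejection under a 0.3 log10 baseline gap and no difference in response is 7-11%. In the one such run without a floor it is 5%. The floor therefore costs something, but far less than the choice of scale.

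**The case against.** The strongest reply is that the article never says IU/mL is used. The word levels is silent on scale, and transformation, detection-limit coding and covariates are often settled in an analysis plan, which is not shown here. A reader might infer that the sponsor has chosen the raw scale. The text does not support that, so every IU/mL result above is conditional. What remains is that the article does fix a model: a linear form, its fixed effects without baseline HBsAg, and the variable. Followed as worded, it gives the IU/mL analysis.

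The clause on distribution-based methods is a partial answer, since it shows that the distribution will be examined. But it names no log scale and no limit rule, and its rank tests cannot replace an interaction with time.

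A reader might also infer that the study will report a spurious group difference. That needs unequal baselines as well as the raw scale, and the article gives no baseline HBsAg by group. With equal baselines the raw-scale test does not over-reject; the harm is lost power.

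Nor do the documents support saying that the floor hides half of the true difference. Such a figure depends on an assumed distribution below an assumed limit, where nothing is observed. Clearance is in any case analysed separately as the primary outcome.

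Finally, a censored model is one of several acceptable choices, and the GEE has a stated purpose. Neither is an error to be corrected.

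**Conclusion.** The point holds as a defect in how one secondary outcome is specified. For an outcome that ranges from barely detectable to 1,500 IU/mL, with 47.5% of patients expected at the floor, the article sets a linear model on levels with no log scale, baseline term or limit rule. Fitted that way, it would have almost no power for the effect the study is planned around (about 5-10%, against 87-98% on log10). With a 0.3 log10 baseline gap and no difference in response, it would reject in about 57-72% of trials.

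The 47.5% follows from the article's planning rates, which are expectations and not data. The simulated figures rest on the assumed assay limit, baseline distribution and declines, and on a slope comparison in place of the full mixed model, so they should be read as illustrative ranges. The Kaplan-Meier and log-rank analysis of clearance and the sample size are untouched. The change is worth making before the efficacy comparison scheduled for 2026, but it does not threaten the primary result.

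**What to change.** Define the 48-week decline as change from baseline in log10 HBsAg. Model log10 HBsAg with visit (weeks 12, 24, 36 and 48) as a factor, group, group-by-visit interaction and baseline log10 HBsAg. Report the adjusted group difference at week 48 with a 95% confidence interval as the main result.

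State the assay limit and the value assigned to results below it in the main model. Add a left-censored (Tobit) mixed model as a sensitivity analysis. The GEE may stay if the text says which of the two models is the main one.

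The cost is a few sentences and one additional analysis, which may need software beyond SPSS 27.0. No extra data, visits or patients are needed.
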